# Improving end-of-life care in acute geriatric hospital wards using the Care Programme for the Last Days of Life: study protocol for a phase 3 cluster randomized controlled trial

**DOI:** 10.1186/s12877-015-0010-7

**Published:** 2015-02-22

**Keywords:** Cluster randomized controlled trial, Terminal care, Hospital, Older people

## Abstract

**Background:**

The Care Programme for the Last Days of Life has been developed to improve the quality of end-of-life care in acute geriatric hospital wards. The programme is based on existing end-of-life care programmes but modeled to the acute geriatric care setting. There is a lack of evidence of the effectiveness of end-of-life care programmes and the effects that may be achieved in patients dying in an acute geriatric hospital setting are unknown. The aim of this paper is to describe the research protocol of a cluster randomized controlled trial to evaluate the effects of the Care Programme for the Last Days of Life.

**Methods and design:**

A cluster randomized controlled trial will be conducted. Ten hospitals with one or more acute geriatric wards will conduct a one-year baseline assessment during which care will be provided as usual. For each patient dying in the ward, a questionnaire will be filled in by a nurse, a physician and a family carer. At the end of the baseline assessment hospitals will be randomized to receive intervention (implementation of the Care Programme) or no intervention. Subsequently, the Care Programme will be implemented in the intervention hospitals over a six-month period. A one-year post-intervention assessment will be performed immediately after the baseline assessment in the control hospitals and after the implementation period in the intervention hospitals. Primary outcomes are symptom frequency and symptom burden of patients in the last 48 hours of life.

**Discussion:**

This will be the first cluster randomized controlled trial to evaluate the effect of the Care Programme for the Last Days of Life for the acute geriatric hospital setting. The results will enable us to evaluate whether implementation of the Care Programme has positive effects on end-of-life care during the last days of life in this patient population and which components of the Care Programme contribute to improving the quality of end-of-life care.

**Trial registration:**

ClinicalTrials.gov Identifier: NCT01890239. Registered June 24th, 2013.

## Background

Pain and symptom management, appropriate treatments and medication and communication about end-of-life issues are identified as key elements of quality care for terminally ill patients [1]. However, clinicians are often inadequately prepared to diagnose dying effectively [2] or to discuss the likelihood of imminent death with patients and families [3-7]. Studies have also shown that older hospitalized people are less likely to receive appropriate pain control and more likely to receive burdensome interventions at the end of life than their younger counterparts [8-11]. Although end-of-life care has been identified as a priority for older people [8,12] and a large proportion die in hospital [13-15], the quality of end-of-life care for older hospitalized patients is suboptimal, leaving room for improvement [16]. As a significant number of older patients may die within the acute geriatric ward of a hospital, it is an important setting in which end-of-life care could be improved.

To improve the quality of care at the end of life in the geriatric hospital population we developed and successfully piloted the Care Programme for the Last Days of Life ([name], [name], [name], [name], [name], [name], [name]: Development of the care programme for the last days of life for older patients in acute geriatric hospital wards: a phase 0–1 study according to the Medical Research Council Framework, submitted; [name], [name], [name], [name], [name], [name]: Feasibility and preliminary effects of the Care Programme for the Last Days of Life in an older acute hospital population: mixed-methods study of the success of implementation and staff perceptions, in preparation). This programme is based on the Liverpool Care Pathway (LCP) programme, taking into account the concerns regarding the LCP raised in the UK and adapted to the geriatric hospital population and setting ([name], [name], [name], [name], [name], [name], [name]: Development of the care programme for the last days of life for older patients in acute geriatric hospital wards: a phase 0–1 study according to the Medical Research Council Framework, submitted). The Care Programme essentially aims to raise awareness among geriatric health care staff of the importance for improving end-of-life care and to prepare them for a change in end-of-life care, to train staff in delivering good end-of-life care with the support of a multi-professional document called the Care Guide for the Last Days of Life, to support dying geriatric patients with the Care Guide for the Last days of Life, to regularly evaluate the delivered end-of-life care and support and to further educate the staff in delivering optimal end-of-life care. The Care Programme consists of the following documents: (1) the Care Guide for the Last Days of Life, (2) supportive documentation and (3) an implementation guide (Figure 1).

**Figure 1 Fig1:**
[figure not shown]
**The Care programme for the last days of life.** ^1^A multi-professional document that provides a template of care for the last days and hours of life with recommendations on different aspects of care and guidance for the psychological and spiritual support of patients and their families. ^2^This guide assists health care staff in implementing the Care Programme for the Last Days of Life on the geriatric ward during a six-month period.

Although end-of-life care programmes have been developed since the 1990s and have already been implemented in more than 20 countries [17], the available evidence regarding their effectiveness is weak and studies are limited to the cancer population. Two systematic reviews conclude that randomized controlled trials or other well designed controlled studies are needed to obtain additional evidence about the effectiveness of end-of-life care pathways [18]. To date, only one cluster randomized controlled trial has been performed to study the effects of the LCP in oncology patients dying in Italian hospitals [19,20]. Results of that study show that a well-implemented LCP programme has the potential to reduce the gap in quality of care between hospices and hospitals. However, the results also show that the effects of the LCP programme are smaller than those shown in qualitative and before-and-after non-controlled studies, and no significant effects on the overall quality of care were found [20]. Nonetheless, the effectiveness of the LCP programme was evaluated in a cancer population whereas end-of-life care pathways or programmes are often used for patients who are dying from diseases other than cancer. Furthermore, the study was underpowered and therefore may have led to underestimated results.

Although it is now widely accepted that clinical practice should be, wherever possible, evidence-based, clinical pathways to improve the quality of end-of-life care are often implemented without a thorough evaluation of their effectiveness [21]. Additional and robust evidence is required [18,22] before realizing a large scale implementation of an end-of-life care pathway. Hence, a thorough evaluation of the effectiveness of the Care Programme for the Last Days of Life is needed before implementing it in practice. We will therefore evaluate the Care Programme in a phase 3 trial according to the MRC framework [23].

The aim of this article is to describe the research protocol of the cluster randomized controlled trial that will be performed to evaluate the effectiveness of a complex intervention, the Care Programme for the Last Days of Life, in acute geriatric wards.

## Methods

### Trial design

While a classic randomized clinical trial is known as the most appropriate method to study the effect of an intervention, it is impossible to randomize a complex intervention within a hospital without contamination of the control arm [24]. For this reason, a multicentre two arm cluster randomized controlled trial will be performed. To prevent possible bias at the level of the hospital, a clustering will take place on the hospital level. Consequently, randomization will be carried out at the level of the hospital. The flow diagram of the study protocol is outlined in Figure 2. The CONSORT guidelines have been followed to design this study [25]. The trial is registered in ClinicalTrials.gov, identifier NCT01890239.

**Figure 2 Fig2:**
[figure not shown]
**Flowchart of the cluster randomized controlled trial.**

### Study population

The inclusion criteria of the hospitals in the trial are:○ the cluster or hospital has one or more acute geriatric wards○ the medical and nursing head of one or more acute geriatric wards per hospital give consent for participation in the study

The inclusion criteria of patients are:○ those dying in the acute geriatric ward between October 2012 and March 2015○ those that having been hospitalized for more than 48 hours○ those having given informed consent at admission for the use of their personal information from medical or nursing records for the purposes of the study.

### General procedures of the cluster RCT

First, a one-year baseline assessment will be conducted in all participating acute geriatric wards of participating hospitals. During that period care will be provided as usual. At the end of the baseline assessment all participating hospitals with one or more participating wards will be randomized into intervention or control groups. In the intervention group the Care Programme for the Last Days of Life will be implemented over a six-month period with the support of an implementation guide (Figure 2). After the implementation period, the intervention group will conduct a one-year post-intervention assessment during which the Care Guide for the Last Days of Life will continue to be used. The control group will continue to provide care as usual and will conduct a one-year post-intervention assessment directly following the one-year baseline assessment (Figure 2).

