## Discussion

This will be the first cluster randomized controlled trial to evaluate the effectiveness of the Care Programme for the Last Days of Life for the acute geriatric hospital setting. Following a baseline assessment, geriatric hospital wards will be randomized to the intervention or control group where the Care Programme will be implemented or care will be provided as usual. A post-intervention assessment should allow us to detect differences in the symptom frequency and symptom burden between patients in the intervention wards and those in the control wards.

A cluster RCT design has several important strengths. The first advantage of this robust design is that a control group will be used. Working with control hospitals can avoid the situation where differences between the baseline and post- intervention assessments within the intervention group are caused by changes other than the intervention that is being studied. Secondly, in all participating hospital wards the quality of care and the quality of life during the last 48 hours of life will be assessed before and after implementation of the care programme. That means that we will be able to compare end-of-life care in geriatric hospital wards before and after the implementation of our intervention, and that each hospital operates as its own control. A third strength of this design is that cluster randomized trials, unlike individually randomized controlled trials, can reduce the effect of treatment contamination as one or more geriatric wards from one hospital will handle the same care principles [34]. Fourth, this design may also increase compliance due to group participation.

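### Control hospitals' outcome year starts six months before the intervention hospitals', so arm is partly confounded with calendar time

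*Protocol article*

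**What the plan says.** The schedule is in the protocol article under General procedures of the cluster RCT. It begins with a common year: "First, a one-year baseline assessment will be conducted in all participating acute geriatric wards of participating hospitals". Allocation follows: "At the end of the baseline assessment all participating hospitals with one or more participating wards will be randomized into intervention or control groups". The arms then diverge. For the intervention arm, "In the intervention group the Care Programme for the Last Days of Life will be implemented over a six-month period", and only then: "After the implementation period, the intervention group will conduct a one-year post-intervention assessment". For the control arm: "The control group will continue to provide care as usual and will conduct a one-year post-intervention assessment directly following the one-year baseline assessment".

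The abstract gives the same timing for the second assessment: "immediately after the baseline assessment in the control hospitals and after the implementation period in the intervention hospitals". The Study population section admits "those dying in the acute geriatric ward between October 2012 and March 2015".

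The Discussion lists the control group as a strength: "Working with control hospitals can avoid the situation where differences between the baseline" and follow-up measurements reflect influences apart from the programme. The limitations that follow do not mention the difference in timing. The primary model, under Multivariable analysis, takes account of clustering by hospital and of the baseline level.

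**The concern.** A control group removes changes over time to the extent that it is observed over the same period as the intervention group. Here the outcome periods are offset by design, and the offset depends on arm. Randomisation cannot balance it. Adjustment for the baseline year removes stable differences between hospitals, but the interval from baseline to outcome differs between arms, so part of any trend stays in the comparison.

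The primary contrast is exposed. The outcomes are retrospective ratings by nurses and family carers, and the article's Background says that the programme was shaped by concerns about an existing end-of-life pathway. A change in usual end-of-life practice during the trial is therefore conceivable. The sample-size section treats a higher EOLD-CAD score as the benefit, so an improving trend would flatter the programme and a worsening trend would hide an effect.

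**Working it through.** **1. The plan's own figure.** Inputs from Sample size calculation: standardised effect 0.55, two-sided alpha 0.05, ICC 0.05, m = 30 patients per cluster, k = 6 clusters per arm. The standard error in SD units is √[2(1 + (m − 1)·ICC)/(k·m)] = √[2 × 2.45/180] = 0.165. The non-centrality is 0.55/0.165 = 3.33. A t-test on 2(k − 1) = 10 degrees of freedom has power 0.851; with k = 5 it is 0.760. Twelve hospitals is therefore the smallest even number reaching 80%, as the article states. The same method reproduces all 12 cells of Table 3, so the sample size is not in dispute.

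**2. Calendar.** October 2012 to March 2015 inclusive is 30 months = 12 + 6 + 12. Allocation is unknown until baseline ends, so any hospital may need all 30 months, and the window leaves no room for late starts.

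| Period | Control | Intervention |
|---|---|---|
| Baseline (months 1–12) | Oct 2012 – Sep 2013 | Oct 2012 – Sep 2013 |
| Implementation (months 13–18) | none | Oct 2013 – Mar 2014 |
| Outcome year | months 13–24: Oct 2013 – Sep 2014 | months 19–30: Apr 2014 – Mar 2015 |

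The overlap is months 19–24 (April to September 2014), 6 of 12 in each arm. Control-only months are October 2013 to March 2014; intervention-only months are October 2014 to March 2015.

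**3. Degree of confounding.** The mean shift is 6 months. With deaths spread evenly, the variance of month within an arm is (12² − 1)/12 = 11.92 and the between-arm component is (6/2)² = 9. The squared correlation of arm with month is 9/20.92 = 0.43, so r is about 0.66.

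**4. What baseline adjustment leaves.** Mid-baseline to mid-outcome is 12 months in control and 18 in intervention. Under linear drift the control arm removes 12/18, or two-thirds, of the change seen in the intervention arm. Six months' worth remains.

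**5. Size.** Bias = yearly drift × 0.5. The drifts are assumptions; the documents give none. The implied SD is 3.2/0.55 = 5.82. The last column is the two-sided rejection rate with no true effect, for 12 hospitals, 30 deaths each and ICC 0.05 (nominal 5%).

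| Assumed drift, points/year | Bias, points | Share of 3.2 | Rejection rate |
|---|---|---|---|
| 0.5 | 0.25 | 8% | 5.6% |
| 1 | 0.5 | 16% | 7.6% |
| 2 | 1.0 | 31% | 15.7% |

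**6. Cost of repair by analysis.** A linear calendar term inflates the variance of the arm effect by 1/(1 − 0.43), about 1.76, if patients are treated as independent. With a hospital intercept the slope is estimated within hospitals, and at ICC 0.05 the inflation is smaller: 1 + [36 × 0.95/(360 × 11.92)]/0.0272 = 1 + 0.0080/0.0272, about 1.29.

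Restricting to the six shared months leaves about 15 deaths per hospital. Power by the method of step 1 is then:
- ICC 0.05: 0.72 with 12 hospitals, 0.62 with 10
- ICC 0.02: 0.84 with 12 hospitals, 0.74 with 10

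**The case against.** Most of the defence limits the size of the problem, and these parts stand.

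- A reader might infer that a control group measured earlier removes no change over time. The documents do not support that. Half of each outcome year is concurrent, the baseline year is common, and under linear drift two-thirds of the change is removed. The Discussion's claim is incomplete, not empty.
- A reader might infer a seasonal imbalance between a control winter and an intervention winter. There is none: each arm covers all twelve calendar months, and both non-shared halves run October to March. Only a difference between those two particular winters could matter, and the drift table does not measure such an event.
- Fatigue with the questionnaires is weak support. It would follow months of data collection more than calendar date, and in both arms the outcome year is the second assessment year.
- Model terms are commonly left to an analysis plan, which is not shown. That the article names no calendar-time term does not show that none was planned, and this point does not rest on it.
- No drift is given. At 0.5 or 1 point per year the false-positive rate moves only to 5.6% or 7.6%.

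What the defence does not answer is the schedule itself. It is stated twice, and the time needed for implementation explains why the intervention arm starts late, not why the control arm must start early.

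**Conclusion.** The point holds as partial confounding of arm with calendar time. Six of 12 outcome months in each arm are non-concurrent, the mean shift is six months, and six months of any drift stays in the primary contrast after baseline adjustment. The six-month offset is stated outright; the calendar dates assume that every hospital uses the full 30-month window.

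The bias could go in either direction and its size is unknown: 0.25 to 1.0 EOLD-CAD points if usual care drifts by 0.5 to 2 points per year. A reader might take the upper figure, 31% of the target difference, as an estimate of actual bias. It is not, because nothing in the documents indicates a drift of that size. The weakness merits correction because it bears on the primary comparison and can be avoided by design at modest cost.

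**What to change.** **By design.** Start the control hospitals' one-year post-assessment on the same date as the intervention hospitals', after the same six-month gap (April 2014 to March 2015 on the inferred calendar). Overlap rises from 6 to 12 months and the mean shift falls to zero. Each hospital still contributes 12 months and about 30 deaths, so the stated power, the number of clusters and the end date do not change. The cost is keeping control wards engaged through a six-month gap.

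**If control collection has already run.** This is likely, since the article is dated 22 February 2015 and the inferred control year ended in September 2014. In that case, before analysis:
- Pre-specify a sensitivity analysis with a calendar-time term in the multilevel model, and state its cost in precision (variance inflation of about 1.76 for a linear term ignoring clustering).
- Pre-specify a sensitivity analysis restricted to deaths in April to September 2014, and state its reduced power (about 0.72 with 12 hospitals and 0.62 with 10 at ICC 0.05), so that a non-significant result there is not read as contradicting the main analysis.

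**In the text.** Qualify the Discussion's claim about what the control hospitals rule out, and add the six-month offset to the limitations.

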### Intervention

The Care Programme aims to introduce and embed the Care Guide for the Last Days of Life, which will be initiated when a patient is diagnosed as dying and which provides a comprehensive template of evidence-based, multidisciplinary care for the last days and hours of life. The Care Programme will be implemented and subsequently established according to an implemention guide incorporating nine components: (1) establishing the implementation project and preparing the environment for organizational changes, (2) preparing the documentation, (3) baseline review, (4) training geriatric health care staff, (5) use of the Care Guide for the Last Days of Life with intensive support, (6) semi-intensive support, (7) evaluation, (8) consolidation and (9) ongoing education, training and support (Table 1).

**Table 1 Tab1:** **Overview of the nine components within the implementation guide**

**N°**	**Content**
**Component 1**	**Establishing the implementation project and preparing the environment**
	▪ Informing the geriatric health care staff about the implementation project and the importance of change in care during the last days of life
	▪ Executive endorsement: acquiring management approval for the trainings and audits
	▪ Involvement of specialist palliative care services is recommended: at least one member of the Palliative Support Team of the hospital is member of the steering group
	▪ Facilitators: a nurse and a physician of the geriatric ward
	▪ Formation of steering group: at least four people from the geriatric ward (facilitators included)
	▪ Intensive 2-day training of facilitators
**Component 2**	**Preparing the documentation**
	▪ Development of an information leaflet for family carers about the facilities in the geriatric hospital ward
**Component 3**	**Baseline review**
	▪ Analyzing end-of-life care data of deceased geriatric hospital patients using the patients’ medical files
**Component 4**	**Training geriatric health care staff**
	▪ Feedback of the results to the staff and focusing on improvement within the geriatric ward
	▪ Facilitators and specialist palliative care colleagues train geriatric health care staff with the aid of a training package (i.e. hand-outs with information about the Care Guide for the Last Days of Life, a copy of the Care Guide for the Last Days of Life, a casus to discuss in group etc.)
**Component 5**	**Care Guide use and intensive support**
	▪ Care Guide use after sufficient training and education
	▪ Intensive support and supervision by the steering group through repeated coaching, telephone and direct guidance, discussion of clinical cases and clinical audits
**Component 6**	**Semi-intensive support**
	▪ Semi-intensive support and supervision by the steering group through repeated coaching, telephone and direct guidance, discussion of clinical cases and clinical audits
**Component 7**	**Evaluation**
	▪ To organize a qualitative evaluation of the implementation: evaluating and discussing the performance and progress of each of the previous components
	▪ The qualitative evaluation acknowledges areas where further support, education or training is needed
**Component 8**	**Consolidation**
	▪ To adopt a strategy to maintain/improve the implementation and sustainability of the Care Guide
	▪ Support and supervision by the steering group through repeated coaching, telephone and direct guidance, discussion of clinical cases and clinical audits
**Component 9**	**Ongoing education, training and support**
	▪ Keeping up to date with developments in end-of-life care and a continuing education and evaluation within the hospital ward

The development and content of the Care Programme for the Last Days of Life are extensively described elsewhere ([name], [name], [name], [name], [name], [name], [name]: Development of the care programme for the last days of life for older patients in acute geriatric hospital wards: a phase 0–1 study according to the Medical Research Council Framework, submitted).

